### The INCUR study

#### Hypotheses and objectives

The INCUR project is specifically aimed at retrieving data from routine clinical practice in order to estimate the incidence of pneumonia events in older persons living in a sample of French nursing homes. Moreover, INCUR is designed to estimate the clinical and economical consequences of pneumonia events by measuring the subsequent access to medical procedures and resources. More in details, the following hypotheses have driven the rationale and conception of the INCUR project:

Primary hypotheses:

a. Pneumonia is a clinical condition frequently complicating the nursing home stay of older persons;

Secondary hypotheses:

a. The onset of a pneumonia event in institutionalized older residents is associated with higher healthcare costs;

b. Incident pneumonia events are associated with an increased risk of mortality in older persons living in nursing home;

c. The onset of a pneumonia event is responsible for a significant worsening of the physical function of nursing home residents;

Tertiary hypotheses:

a. Specific variables at patient- and nursing home-level may predict the severity of the pneumonia-related functional loss;

b. Nursing home residents dying due to pneumonia produce a significantly higher burden in terms of healthcare costs compared to nursing home residents dying for other causes.

Therefore, the INCUR project will pursue the following aims:

Primary aims:

a. To estimate the incidence of pneumonia events in a sample of older nursing home persons over a period of 12 months;

Secondary aims:

a. To compare the healthcare costs of nursing home older persons experiencing a pneumonia event versus those who will not over a period of 12 months;

b. To calculate the mortality risk in a sample of older residents living in nursing home according to the presence/absence of a pneumonia event occurred during a follow-up period of 12 months;

c. To measure the physical function modifications experienced by a sample of nursing home residents according to the presence/absence of a pneumonia event occurred during a follow-up period of 12 months;

Tertiary aims:

a. To identify sociodemographic, clinical, and biological characteristics of nursing home older residents, as well as environmental and organizational factors of their own hosting institution, which are associated with a higher degree of functional loss following a pneumonia event;

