c. When a pneumonia event will occur, physical function information collected after its onset will be compared to those previously recorded. The difference in physical function measured before and after the pneumonia event will be adjusted for the days between the event onset and the following physical function assessment. This analytical approach will allow to take into account the negative influence that the presence of a (sub)acute phase of the respiratory process may exert on physical function if the event will occur close to the evaluation. Mixed effects analysis of covariance models will also be performed to evaluate physical function modifications over time between patients who experienced a pneumonia event versus those who did not. If statistical power will be sufficient, stratified analyses will also be performed according to the severity of the pneumonia event (e.g., events requiring hospitalization versus those who did not).

For the present analyses, the sum of the results from the three SPPB categorized tests (ranging from 0 [worst physical performance] to 12 [best physical performance]) as well as the crude timed results obtained from each single assessment (in seconds) will be used for the analyses. This will allow to evaluate whether the pneumonia event will differently affect specific components of physical performance (i.e., balance, muscle strength, or gait/coordination).

Tertiary aims:

a. Chi-square and t-test analyses will be performed to describe the study population for main sociodemographic, behavioral, and clinical characteristics according to the presence/absence of a pneumonia event occurred during the INCUR project follow-up. Mann-Whitney U statistics will be used for non-normally distributed continuous variables. Normalization through log-transformation will be used for non-normally distributed study variables. Subsequent unadjusted and adjusted Cox proportional hazard models will be analyzed to identify patients’ characteristics that are able to significantly predict pneumonia events (dependent variable of interest). Among the covariates, age, gender, race, and preexisting respiratory conditions will always be considered as potential confounders. Age, gender, and race interactions will be tested for the studied relationships by adding specific interaction terms into the models. If possible, stratified analyses will be performed whereas significant interactions will be obtained.

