A similar analytical approach will be used to evaluate specific characteristics of the EHPADs as significant determinants of pneumonia events in patients. EHPADs and patients’ characteristics might be combined in secondary analyses to evaluate the additive value of specific parameters towards the onset of pneumonia events.

b. We will perform restricted analyses in participants who will die during the follow-up (expected mortality about 20% over 12 months, that is 160 fatal events in our sample population). This subsample of participants will be divided according to the cause of death (i.e., pneumoniarelated versus other causes [expected number of cases 11.2 versus 158.8 according to Rothan- Tondeur et al [38]). Chi-square and t-test analyses will be performed to verify whether significant differences between patients dying because of a pneumonia event versus those dying for other causes exist for the following healthcare parameters: - Total expenditure (in Euros) that participants will cost to the healthcare system over the follow-up period. This datum will be obtained by the Gerontopôle from the *Caisse Primaire d’Assurance Maladie*, which has allowed the specific and exclusive release of it to the CHUToulouse. Additional analyses will also consider specific aspects of the direct healthcare costs of INCUR participants such as expenses due to hospitalizations or physical therapy sessions.

Mann-Whitney U statistics will be used for non-normally distributed continuous variables. Normalization through log-transformation will be used for non-normally distributed study variables. These analyses will consider the entire follow-up period available. Secondary analyses will also be restricted to consider the last month preceding the fatal event. In this way, we will be able to undestand whether the hypothesized higher healthcare costs of pneumonia events leading to death are distributed over time, or compressed in the very last period of life. If the statistical power will be sufficient, additional adjusted logistic and linear regression models will be performed taking into account potential confounders.

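### The analyses under tertiary aim a model who gets pneumonia, whereas the aim asks which factors go with greater functional loss after it

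*Protocol article*

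**What the plan says.** In the protocol article, under Hypotheses and objectives, tertiary hypothesis a is: "Specific variables at patient- and nursing home-level may predict the severity of the pneumonia-related functional loss". The matching tertiary aim a seeks resident characteristics and features of the institution "which are associated with a higher degree of functional loss following a pneumonia event". Both make functional loss the outcome, and both presuppose that a pneumonia has occurred.

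The Analysis plan, under Tertiary aims, a, starts with descriptive tests that split the study population "according to the presence/absence of a pneumonia event occurred during the INCUR project follow-up". It then fits Cox models to find patient characteristics "that are able to significantly predict pneumonia events (dependent variable of interest". The same approach is used to "evaluate specific characteristics of the EHPADs as significant determinants of pneumonia events in patients", and resident and home data may be combined "to evaluate the additive value of specific parameters towards the onset of pneumonia events".

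Secondary analysis c is the only place where functional change is analysed. It compares function before and after an event, adjusting for the days from onset to the next assessment. It also fits mixed models contrasting residents with and without pneumonia. If power allows, it stratifies by severity of the event, for example by whether hospitalisation was needed.

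**The concern.** Factors that raise the chance of catching pneumonia need not be those that worsen decline once it has occurred. A resident or home characteristic could matter for one and not for the other. If the plan is carried out as described, the hypothesis on functional loss is never tested, while an onset analysis that no listed aim requests is carried out under its label.

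Functional loss is not a side issue in this study: Methods/design justifies excluding GIR 1 residents on the ground that loss due to pneumonia could not be determined in them. The analysis population is also at stake. Onset can be modelled in the whole cohort, but loss after pneumonia only among cases, so the information available is much smaller than 800 residents suggests.

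**Working it through.** **Step 1. Aim and analysis side by side.**

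| Item | Outcome | Population | Predictors |
|---|---|---|---|
| Tertiary hypothesis a and aim a | Degree of functional loss after pneumonia | Residents who had pneumonia | Resident and home factors |
| Tertiary a, chi-square, t and Mann-Whitney tests | None; groups defined by pneumonia yes/no | Whole cohort | Not applicable |
| Tertiary a, Cox models | Pneumonia event | Whole cohort | Resident factors |
| Tertiary a, home-level and combined analyses | Pneumonia event or its onset | Whole cohort | Home factors, alone or with resident factors |
| Secondary c, before/after comparison | Functional change | Residents with pneumonia | Days since onset only |
| Secondary c, mixed models | Function over time | Whole cohort | Pneumonia yes/no |

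No analysis row combines the outcome and the predictors of the first row. Tertiary a has the predictors with the wrong outcome; secondary c has the outcome without the predictors. The optional stratifier in c, severity of the episode, describes the event and is not one of the resident or institutional factors in the aim.

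**Step 2. Size of the right analysis set.** Inputs are from Sample size analyses: 800 residents, 365 days, 20% yearly mortality, US rates of 0.3 to 2.3 per 1,000 resident-days, and a French survey with 22 pneumonias in 2,140 residents over 28 days.

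- Resident-days: 800 × 365 = 292,000.
- US rates: 292,000 × 0.8 × 0.3/1,000 = 70.08 (stated 70.1); 292,000 × 0.8 × 2.3/1,000 = 537.28 (stated 537.3).
- French survey: 22/2,140 × 800 × 365/28 = 107.21 (stated 107.2, before any reduction).
- With 20% mortality and 40% fewer events over half the year: 107.21 × 0.8 × 0.8 = 68.61 (stated 68.6).

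All four figures reproduce. They count events. The primary analysis allows for residents with more than one event, and a resident who dies before the next six-monthly visit has no later assessment. Each count is therefore an upper limit, within its scenario, on the residents who can contribute a change score.

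**Step 3. Illustration of what such a set can show.** Assume 80% power (not in the article), two-sided 5% alpha, one predictor and no clustering. The smallest detectable correlation is tanh[(1.960 + 0.842)/√(n − 3)].

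- n = 68.6: 0.33. n = 107.2: 0.27.
- If only 60% of cases can be reassessed (assumed): n = 41.2 gives 0.43 (0.425 before rounding), and n = 64.3 gives 0.34.
- At the upper US figure, n = 537.3: tanh(2.802/√534.3) = 0.12.

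The mismatch in Step 1 does not depend on these figures. They show only why the predictor list must be short if the lower counts apply.

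**The case against.** The strongest defence is that a journal article condenses the full plan, and that secondary analysis c already does most of the work. It builds the before/after change among cases and adjusts for time since onset, so what is missing is one predictor step. The second half of this stands, and it makes the repair small. The first half does not: the article does not leave the outcome open but names pneumonia events as the dependent variable, and then repeats that outcome for the homes. An unseen document could add a model but would not make this text consistent.

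Several stronger readings are tempting, and the article does not support them.

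- A reader might infer that the study's main conclusions are at risk. The only primary aim is incidence; that aim, the secondary aims and the sample size are unaffected.
- A reader might infer that functional decline goes unanalysed. Secondary c analyses it; only its predictors are missing.
- A reader might expect predictors of onset to be reported as predictors of decline. The plan labels the dependent variable openly, so this is speculation.
- A reader might take about 70 to 107 as the number of analysable residents. Those are event counts, and the US range reaches 537.3.
- A reader might assume that every variable needed is already collected. Table 2, which lists main areas only, shows no laboratory or institution-level item, although the aim names biological, environmental and organisational factors. They may be collected, but the article does not show it.

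**Conclusion.** The point holds: the analyses described under tertiary aim a cannot answer tertiary aim a, and no other analysis in the article does. Within that aim the mismatch is complete, since both outcome and population differ. It should be fixed, but it is not critical to the study, because one of two tertiary aims is affected and the primary estimate is not. The conclusion rests on the text alone. The size of the correct analysis set remains uncertain: at most 68.6 to 107.2 on the French figures or 70.1 to 537.3 on the US figures, less recurrences and cases who die before reassessment. Modelling predictors of onset is legitimate in itself; it is just not what this aim asks.

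**What to change.** Under tertiary aim a, extend the before/after analysis of secondary aim c. Among residents with a pneumonia event and a later assessment, regress post-event functional change on a short, prespecified list of the resident and home characteristics that the study actually collects. Adjust for pre-event function and for days since onset, and allow for clustering within the 13 homes. Keep the home-level list especially short, since it rests on 13 units. Report how many cases died before they could be reassessed.

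Relabel the existing Cox models as an exploratory analysis of predictors of pneumonia onset. Alternatively, if onset was the intended question, reword tertiary hypothesis a and aim a to match the Cox models; this also restores consistency, but gives up the question on functional loss.

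The cost is revised wording and one additional model. Function is already assessed at baseline, 6 and 12 months, and events are already recorded, so no extra visit is needed. Before the list is fixed, the study team should confirm which biological and institution-level variables exist. The mid-term visits were still under way when the article was written, so the change could be made before the 12-month data were complete.

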Each eligible participant will be followed-up for 12 months with a total of three clinical assessments: at baseline, 6 months (mid-term visit), and 12 months (close-out visit). The timeline of the INCUR project is depicted in Figure 1. Recruitment of participants and baseline visits began in February 2012 and ended in July 2012, after a preliminary organization phase (for coordinating activities of researcher with the participating nursing homes). The mid-term visit of participants (after 6 months of follow-up) is currently ongoing.

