### Sample size analyses

Mehr and colleagues [25] estimated that the incidence of nursing home-acquired pneumonia in the United States may range between 0.3 to 2.3 episodes per 1,000 resident-days. In the present study, we expect to enroll 800 EHPAD residents and follow them over a 12-month period (i.e., a total of 292,000 resident-days). Considering the attrition due to mortality (i.e., 20% per year in this setting^4^), we may expect between 70.1 and 537.3 cases according to the Meher and colleagues’ data [25]. More recently, Rothan-Tondeur and colleagues [38] reported 311 infections in a sample of 2,140 nursing home residents over a period of 28 days (from January 24 to February 20, 2005). The study was conducted defining pneumonia according to the same criteria we will implement in INCUR. Authors showed that pneumonia represented the 7% of all the cases of infections (i.e., 22 events). Translating these figures over a 365-day period (as proposed in the INCUR project) and sample size we plan to recruit (i.e., 800 participants), we obtain 107.2 pneumonia events. It might happen that attrition due to mortality (i.e., 20% per year^4^) and the spring-summer seasons (during which the pneumonia events might be fewer; i.e., additional 40% over 6 months) may further reduce such estimation. However, we believe that, even in the worst case scenario (i.e., 68.6 cases of pneumonia over one year, consistent with the minimum estimation obtained from analyses performed on the Meher and colleagues’ data [25]), it will be possible the evaluation of a sufficient number of events to successfully accomplish the INCUR study aims. The recruited sample size of 800 participants produces a two-sided 98.2% or 95.2% confidence interval with a width equal to 0,050 when the incidence of pneumonia are 10% or 15%, respectively. Such incidence rates are overestimating the outcome of interest compared to the previous study by Rothan-Tondeur et al [38]. (7%); thus, INCUR study is adequately powered to accurately estimate the incidence of pneumonia with the sample of 800 participants.

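### Tertiary aim b compares raw total cost from baseline to death, so any difference in time to death by cause enters the cost contrast; the bias from the plan's own figures is small and the remedy cheap

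*Protocol article*

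**What the plan says.** All of this stands in the Protocol article, Analysis plan, tertiary aim b, unless another section is named.

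- Population: "We will perform restricted analyses in participants who will die during the follow-up".
- Outcome: "Total expenditure (in Euros) that participants will cost to the healthcare system over the follow-up period". This is a sum, not a rate.
- Main window: "These analyses will consider the entire follow-up period available".
- Main test, pneumonia deaths against all remaining deaths: "Chi-square and t-test analyses will be performed to verify whether significant differences between patients dying because of a pneumonia event versus those dying for other". Mann-Whitney or log-transformation is used for non-normal variables.
- Secondary window: "Secondary analyses will also be restricted to consider the last month preceding the fatal event". Its stated purpose is to see whether the excess cost is spread over time or concentrated at the end of life.
- Adjustment: "If the statistical power will be sufficient, additional adjusted logistic and linear regression models will be performed taking into account potential confounders". Time to death is not named.

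Two other places bear on timing. Methods/design says "Recruitment of participants and baseline visits began in February 2012 and ended in July 2012". Sample size analyses allows for "spring-summer seasons (during which the pneumonia events might be fewer; i.e., additional 40% over 6 months".

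**The concern.** Everyone in this analysis dies, so each person's cost window closes at his or her own death. A resident who dies in month 11 has had many more days in which to incur ordinary costs than one who dies in month 1. The starting point is a study visit, not the onset of an illness, so the length of the window is largely a product of the enrolment date. A t-test or Mann-Whitney test on the raw total takes no account of it.

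Two consequences follow. If time to death differs by cause, part of the cost difference reflects when people died rather than why. If it does not differ, the unequal windows still add variance to a comparison in which one group is expected to hold about 11 people. The plan already adjusts for elapsed days in secondary aim c, where functional change is corrected for the days between pneumonia onset and the next assessment. Tertiary aim b has no corresponding term.

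**Working it through.** **1. Group sizes.** Expected deaths: 0.20 × 800 = 160, as the plan states. Pneumonia deaths: 0.07 × 160 = 11.2, as stated. Other deaths: 160 − 11.2 = 148.8. The plan prints 158.8, which makes the groups sum to 170; this is a separate slip. The checks below use 11 and 149.

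**2. Timing difference from the plan's own figures.** The inputs are enrolment February to July, 12 months of follow-up, 20% annual mortality and 40% fewer pneumonia events in spring-summer. Assumptions: enrolment is spread evenly, spring-summer means April to September, pneumonia deaths follow the seasonality of pneumonia events, and daily cost is constant.

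Mean day of death = Σ t·h(t)·S(t) / Σ h(t)·S(t), averaged over enrolment dates. Here S(t) = exp(−λt), λ = −ln(0.8)/365, and h is 1 in October to March and 1 − r in April to September.

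| Spring-summer reduction r | Mean day of death |
|---|---|
| 0 | 175.2 |
| 20% | 179.9 |
| 40% | 185.7 |

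Pneumonia deaths take r = 40%. The document does not say how seasonal other deaths are, so this is shown as a range. With constant daily cost, the ratio of mean totals equals the ratio of mean days:

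- other deaths not seasonal: 185.7 / 175.2 = 1.060 (difference 10.5 days);
- other deaths 20% lower in spring-summer: 185.7 / 179.9 = 1.032;
- other deaths 40% lower: 185.7 / 185.7 = 1.000.

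Spreading deaths evenly over the year, instead of using a mortality hazard, gives 192.6 against 182.5 days: 192.6 / 182.5 = 1.055.

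**3. False-positive rate at that shift.** Simulation: 11 against 149 deaths, identical daily-cost distributions (CV 50% or 100%), pneumonia deaths 40% seasonal, other deaths not seasonal, two-sided 5% tests. The t-test and Mann-Whitney test rejected in roughly 4.4% to 6% of runs.

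**4. What larger shifts would do.** These shifts are assumed, not documented. Daily-cost CV is 0.5 to 1.0, and a terminal cost worth 0 to 180 days of usual cost is added equally in both groups.

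| Pneumonia deaths later by | Ratio of mean totals | t-test rejections |
|---|---|---|
| 0 days | about 1.00 | about 5% |
| 30 days | 1.07 to 1.18 | 8% to 12% |
| 60 days | 1.17 to 1.33 | 15% to 26% |
| 90 days | 1.25 to 1.50 | 24% to 46% |

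**5. Variance, even with equal timing.** Write total = daily cost × days, with days uniform on 0 to 12 months and independent of daily cost. Then E[T²]/E[T]² = 4/3, and the squared CV of the total is (1 + CV²)(4/3) − 1. Relative to CV² this is:

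- CV 50%: (1.25 × 4/3 − 1)/0.25 = 2.67;
- CV 100%: (2 × 4/3 − 1)/1 = 1.67;
- CV 150%: (3.25 × 4/3 − 1)/2.25 = 1.48.

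In the simulations of step 4, time of death alone explained about 19% to 51% of the variance in total cost. The lower values go with more variable daily cost or a larger terminal cost.

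**The case against.** The strongest reply is that late deaths accumulate more cost in both groups, so the contrast is biased only if time to death differs by cause. That is right: with equal timing the ratio is about 1.00 and the tests hold their level. A reader might infer that pneumonia deaths will come out dearer by construction, or that the design is materially tilted towards the hypothesis. The document does not support this. The direction rests on other deaths being less seasonal than pneumonia deaths, on which it is silent. At its own 40% the shift barely moves the rejection rate. Steeper seasonal reductions, or shifts of 30 days or more, are assumptions.

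A second reply is that the last-month analysis already gives nearly equal windows and would be reported alongside. This limits the harm. It does not repair the main comparison, because it is secondary, covers only end-of-life cost, and is meant to interpret a whole-period excess that must first be sound.

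A third reply is that time to death could be among the potential confounders, which an article need not list. True, but those models run only if power is sufficient, which is doubtful with about 11 pneumonia deaths, and the unadjusted test would remain the main result.

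Finally, this is the last tertiary aim, worded as exploratory, in a cohort whose primary aim is incidence. That stands and sets the priority.

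**Conclusion.** The point holds in a limited form. Outcome, window and tests are all stated, and together they let time observed enter the comparison by cause of death. From the plan's own enrolment window and seasonality, the bias is at most about 10 days, or 0 to +6% of total cost, with a false-positive rate near 5 to 6%. This rests on even enrolment, constant daily cost, and a range of 0 to 40% for the seasonality of other deaths. The added variance does not depend on a timing difference, but its size depends on cost distributions that the document does not give. A larger bias is possible only if time to death differs more by cause, and nothing in the document shows that it does. Severity is low: no primary or secondary result depends on this analysis.

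**What to change.** In tertiary aim b:

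1. Make the main comparison a regression of total cost (or log cost) on cause-of-death group that always includes days from baseline to death as a covariate, with no power condition.
2. Estimate the coefficient for days; do not impose a log-days offset. An offset forces cost to be proportional to days alive. If cost is concentrated near death, as the plan itself considers possible, early deaths would then look dear per day and the later-dying group would look cheap.
3. Keep the last-month analysis as support, restricted to decedents observed for the whole month.
4. Report raw totals descriptively, with observed days per group.

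The cost is analysis wording only, since death events and expenditure are already collected. There are two small downsides. The model carries one extra parameter with about 11 pneumonia deaths. The 30-day window also drops early deaths: (1 − 0.8^(30/365)) / 0.20 = 0.09, about 9% of deaths at a constant hazard. For that reason the regression on all decedents should lead. The gain in precision is greatest where daily cost varies little and may be slight where it varies a lot.

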### Analysis plan

All the analyses will consider an alpha value threshold equal to 5% as determining the statistical significance.

Primary aims:

a. Taking into account the 12-month follow-up of the study participants, we will detect all the participants experiencing a new pneumonia event. The ratio between the number of participants experiencing one or more events and the number of participants constituing the overall sample will provide the incidence of pneumonia in the sample population. Results will be presented as pneumonia cases per 1,000 resident-days, and as pneumonia events over one year. Stratified analyses will be performed according to age groups, gender, and pre-existing pulmonary disease.

Secondary aims:

a. Primary independent variable of interest for the present analyses will be the total expenditure (in Euros) that participants will cost to the healthcare system over the follow-up year. Additional secondary analyses will also consider specific aspects of the direct healthcare costs of INCUR participants such as expenses due to hospitalizations or physical therapy sessions. All these analyses will be stratified and compared according to the presence/absence of pneumonia events.

Unadjusted and adjusted analyses of covariance, logistic regression models, and multinominal logistic regression models will be performed to evaluate the means and risks of the outcome variables predicted by the absence/presence of pneumonia events occurred during the follow-up (dicothomous independent variable of interest).

b. Participating patients will be divided in two groups, according to the presence/absence of a pneumonia event experienced during the follow-up period. Then, the risk of death will be calculated and compared between the two groups. Kaplan-Meier survival curves will be provided according to pneumonia events. Moreover, adjusted Cox proportional hazard analyses taking into account age, gender, pre-existing pulmonary disease, and other possible confounders will be performed to estimate the risk of dying in patients who experienced a pneumonia versus those who did not. Follow-up will be censored at the date of death for patients dying during the follow-up, or to the last contact date for those who did not.

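### The two planned cost comparisons among decedents overlap, so they need not show when the excess cost of pneumonia deaths arose

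*Protocol article*

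**What the plan says.** Protocol article, Analysis plan, Tertiary aims, item b, restricts the analysis to residents who die during follow-up ("expected mortality about 20% over 12 months, that is 160 fatal events in our sample population") and splits them by cause of death. The tests are named: "Chi-square and t-test analyses will be performed to verify whether significant differences between patients dying because of a pneumonia event". The comparison group is the residents whose death had another cause. The outcome is a cumulative amount: "Total expenditure (in Euros) that participants will cost to the healthcare system over the follow-up period". Mann-Whitney tests or a log transformation are foreseen for non-normal variables.

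Two time windows are then named. The first: "These analyses will consider the entire follow-up period available". The second: "Secondary analyses will also be restricted to consider the last month preceding the fatal event". The purpose is stated directly: the two windows are meant to tell if the extra spending on pneumonia deaths falls under one or the other of two patterns, given as "are distributed over time, or compressed in the very last period of life". The same section sets the level for every analysis: "All the analyses will consider an alpha value threshold equal to 5% as determining the statistical significance".

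Item b describes no comparison of cost before the last month, no cost per unit of time, and no contrast between the two windows.

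**The concern.** The article does not merely list two analyses. It claims that together they answer a question about timing. To say that the excess is spread over time, one needs evidence of an excess before the last month. The whole-period comparison does not isolate that part, because the last month is included in the total. To say that the excess is compressed, one needs evidence that the earlier period contributes little, and neither comparison estimates that contribution separately.

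What is at stake is one explanatory statement in the report: whether costly pneumonia deaths reflect a long, resource-intensive course or a burst of spending just before death. If both comparisons come out positive, either account could be written with equal justification.

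**Working it through.** **The plan's own figures.** Deaths: 800 × 0.20 = 160, as printed. Pneumonia deaths: 160 × 0.07 = 11.2, as printed. Other deaths: 160 − 11.2 = 148.8, but the article prints 158.8, and 11.2 + 158.8 = 170. This slip does not affect the point; 11 versus 149 is used below. The 7% appears under Sample size analyses as the pneumonia share of infections, so 11 is only a rough planning number.

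**Identity.** With cumulative cost in euros, and zero earlier cost for a resident with no earlier follow-up, mean differences (pneumonia minus other deaths) satisfy:

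whole-period difference = last-month difference + earlier difference.

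- Excess D entirely in the last month: last month D, earlier 0, whole period D.
- Excess D spread evenly over 12 months: last month D/12, earlier 11D/12, whole period D.

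The whole-period difference is D in both cases. The last-month difference is above zero in both cases. Only the earlier difference is zero in one case and not in the other.

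**Recovering the earlier part.** Raw means can be subtracted: whole period minus last month. P-values cannot. Nor can Mann-Whitney results or means of log cost, because neither ranks nor logs of a sum split into those of its parts.

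**Illustration.** The article gives no cost mean, SD or expected excess, so these are assumptions: independent monthly costs with mean 1 and SD 1, normal or lognormal; follow-up before death either 12 months or uniform over 1–12 months; total excess D of 2, 4 or 8 average months' cost; two-sided 5% tests; 1,000 runs per scenario. Entries are the percentage of runs with a significantly higher pneumonia cost, as ranges over both distributions, both follow-up patterns, and the t-test and Mann-Whitney test. With no true difference the expected entry is 2.5%.

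| D | True pattern | Last month | Whole period | Earlier period only (not planned) |
|---|---|---|---|---|
| 2 | last month only | 100 | 27–52 | 2–4 |
| 2 | spread | 7–62 | 28–50 | 18–47 |
| 4 | last month only | 100 | 85–99 | 1–3 |
| 4 | spread | 18–98 | 82–99 | 48–98 |
| 8 | last month only | 100 | 100 | 1–4 |
| 8 | spread | 51–100 | 100 | 93–100 |

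The whole-period column is nearly the same for the two patterns. At D = 8 the whole-period test is always positive, so the chance that both planned tests are positive equals the last-month entry: 100% for a last-month excess and 51–100% for a spread one. The high end comes from the uniform follow-up, where residents dying in the first month carry all their excess there, and from the Mann-Whitney test on lognormal costs. At D = 2 with 12 months of follow-up, both are positive in 41–52% of runs for a last-month excess and in at most 7–13% for a spread one, so there the pair does carry some information.

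**Sensitivity to the cost model.** Under a second set of assumptions (correlated skewed monthly costs, last month at 3 times the base rate, survival uniform over 1–12 months), doubling, tripling or quadrupling last-month cost adds 3, 6 or 9 base months. The whole-period test is then significant in 26–33%, 64–69% and 86–89% of runs, and a test of earlier cost in about 5%. The direction is the same; the size moves with the inputs.

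**Precision.** For one window with 11 versus 149, the standard error in SD units is √(1/11 + 1/149) = 0.312. The 95% half-width is 1.975 × 0.312 = 0.62 SD. The difference detectable with 80% power is (1.975 + 0.842) × 0.312 = 0.88 SD; at 0.5 SD, power is about 36%.

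**The case against.** The strongest reply is that the plan never says a significant whole-period test means a spread excess, or that a non-significant last-month test rules out compression. It says only that the two analyses together will inform the question. That stands: a reader might infer such a rule, but the article does not state one.

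It is also tempting to say that the planned results cannot separate the two patterns. That is too strong. On raw euro means the earlier difference follows by subtraction, and in some configurations the pair of results is informative. What remains is that the article does not say the subtraction will be made, and that it is unavailable from the Mann-Whitney or log-scale results the plan prescribes for non-normal variables.

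A reader might also take the whole-period rejections under a last-month excess as false positives to be set against 5%. They are not. Aim b asks whether total cost is higher, and if the excess falls in the last month, it is. Those rejections are correct answers to aim b; they simply do not date the excess.

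Finally, the low number of pneumonia deaths limits the data whatever analysis is used. The article prints the expected count and makes its adjusted models conditional on power, so this is not a fault in the plan and no fix removes it.

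**Conclusion.** The point holds in a limited form. The two windows are nested, no earlier-period comparison is planned, and two positive results fit both a last-month excess and a spread one. That follows from the identity and needs no cost assumption. How often it would happen does depend on assumptions: the percentages above rest on invented monthly costs and on 11 versus 149 deaths, and should be read as illustration only.

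The main comparison of total cost for aim b is unaffected, as are the primary and secondary aims. This is a secondary analysis inside an exploratory tertiary aim, so the point is minor. It is worth making because the article states that the method will answer the timing question and the correction is cheap.

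**What to change.** Keep the whole-period comparison for aim b. For the timing question, replace the nested pair by two non-overlapping windows: the last month before death, and follow-up before that month. Express cost per day alive in each window, so that length of survival does not drive the earlier figure, and exclude from the earlier window residents with no follow-up in it. Report the pneumonia-versus-other difference in each window and the group-by-window contrast, each with a 95% confidence interval, and base any statement on timing on that contrast.

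Fix the scale in advance and show both the euro difference and the cost ratio. They can disagree when end-of-life care costs more in everyone. For example, if the base rate is 1 before the last month and 3 in it, and pneumonia doubles both, the euro differences are 1 and 3, which looks compressed, while the ratios are 2 and 2, which looks even.

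The cost is a change of wording. The planned last-month analysis already needs costs that can be split by date, so no new data are required. The downside is imprecision: with about 11 pneumonia deaths the contrast may well be inconclusive, and it should then be reported as inconclusive.
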